### Exploratory objectives

Exploratory objectives will help to identify the mechanisms underlying the effect of MSC on neurodegeneration. Whit this aim, the ability of MSC to *in vitro* rescue 6-OHDA damaged neural cell lines and to synthesize and secrete neurotrophines will be measured to determine if these factors are related to the clinical response.

### Study design

All patients over the age of 40 years with diagnosis of “probable progressive supranuclear palsy - Richardson’s disease subtype” according to current diagnostic criteria [4; 9] are eligible (Table 1).

**Table 1 T1:** Inclusion and exclusion criteria

** *Inclusion criteria* **	-Diagnosis of ’probable Progressive Supranuclear Palsy - Richardson’s disease subtype’ according to current diagnostic criteria [4; 9], including akinetic-rigid syndrome;
	-Age at onset ≥ 40 years;
	-Disease duration 12 months to 8 years;
	-Supranuclear ophthalmoplegia;
	-Postural instability or falls within 3 years from disease onset;
	-Positive MRI for PSP criteria (Quattrone et al., [30]);
	-Stable pharmacological treatment for at least 90 days;
	-Lack of response to chronic levodopa (at least 12-month treatment);
	-Able to stand in upright posture without assistance for at least 30 seconds;
	-Written informed consent (including video taping).
** *Exclusion criteria* **	-Idiopathic Parkinson’s disease;
	-Cerebellar ataxia;
	-Symptomatic autonomic dysfunction;
	-Evidence of any other neurological disease that could explain signs;
	-History of repeated strokes with stepwise progression of parkinsonian features;
	-History of major stroke;
	-Any history of severe or repeated head injur;
	-A history of encephalitis;
	-A history of neuroleptic use for a prolonged period of time or within the past 6 months;
	-Street-drug related parkinsonism;
	-Significant other neurological disease on CT-scan/MRI;
	-Oculogyric crises; -major signs of corticobasal degeneration;
	-Signs of Lewy body disease;
	-Other life-threatening disease likely to interfere with the main outcome measure;
	-Any clinically significant laboratory abnormality, with the exception of cholesterol, triglycerides and glucose;
	-Renal failure (serum creatinine >300 mM/L);
	-Transaminase elevation > twice upper limit of normal;
	-Any concomitant disorder associated with bone marrow function impairment;
	-Any concomitant disorder that requires chronic treatment with immunosuppressors, anti-inflammatory agents, and/or growth factors;
	-Dementia (MMSE < 24 according to Folstein 1975 or defined according to DSM-IV TR criteria);
	-Any other disorder that could interfere with the evaluation of treatment or that could make intra-arterial infusion inadvisable;
	-Any other features that, according to the investigator, could reduce adherence to protocol procedures or prevent rapid access in case of emergency;
	-Women of child-bearing age;
	-Participation in another clinical trial with experimental treatment in the last 30 days;
	-Brain MRI evidence of severe vascular abnormalities, space-occupying lesions or normal pressure hydrocephalus.

The first 5 patients are treated in an open phase with autologous MSC therapy with the same procedures as for the randomized phase.

After these first 5 patients have been followed-up for a minimum of 2 months from the cellular infusion, the ISS Data Safety Monitoring Board will review the safety data prior to open the accrual of the subsequent randomized controlled phase.

In the randomized phase the patients undergo to:

–immediate autologous MSC therapy followed by delayed sham or

–immediate sham followed by delayed autologous MSC therapy.

The delay amounts to 6 months and all patients will be followed-up for at least 12 months after MSC therapy, so the total duration of the study is 18 months. The study design is shown in Figure 2.

**Figure 2 F2:**
[figure not shown]
**Study design. A)** Pilot phase; **B)** Randomized study.

### Bone marrow collection and MSC isolation

Bone marrow is aseptically drawn by qualified medical staff at the Bone Marrow Transplantation Centre - Fondazione IRCCS Ca’ Granda Ospedale Maggiore Policlinico Milano according to standard procedures. The maximum quantity of bone marrow to be collected is 30 ml. The isolation of BM MSC is performed under Good Manufacturig Practices (GMP) conditions as requested by European Regulations for cell-based advanced therapy medicinal product (ATMPs) in the “Cell Factory” Laboratory of Fondazione IRCCS Ca’ Granda Ospedale Maggiore Policlinico Milano. The “Cell Factory” was the first public Italian hospital-based facility to receive authorization for the production of ATMPs (Agenzia Italiana del Farmaco – AIFA – authorization n°120/2007 and subsequent confirmations, the last in 2013). The procedures for BM MSC aseptic production and quality control have been developed by the authors. Briefly, unprocessed BM is directly seeded in alpha Modified Eagle Medium supplemented with 10% FBS at the concentration of 50,000 total nucleated cells (TNC)/cm^2^ in Cell Stack Chamber system (Corning, Lowel, MA). After 72 hours, non-adherent cells are removed by washing with PBS (Macopharma, Mouvaux, France) with complete medium change. Medium changes are also performed twice a week. On day 14 (±3) MSC at P0 are detached using 25 mL/layer of TrypLE- Select (Gibco-Life Technologies, Carlsbad, CA, USA) and re-seeded in the same culture conditions at the concentration of 4000 MSCs/cm2. The culture is stopped at 28 days (±3) of culture (passage 2) and the cells are re-suspended in a solution containing normal saline solution with human serum albumin (Kedrion, Castelvecchio Pascoli, Lucca, Italy) 10% (vol:vol) and DMSO (Bioniche Lifesciences, Inc., Belleville, ON, Canada) 10% (vol:vol). The cell product is cryopreserved using a controlled-rate freezer (Nicool Plus, Air Liquide) programmed to freeze at −1 C/ min and is stored in the vapor phase of liquid nitrogen in bags (CryoMACS Miltenyi, Teterow, Germany). The day of the infusion, the cells are thawed at 37°C and resuspended (1:2) in normal saline solution with human serum albumin (Kedrion) 10% (vol:vol) and ACD-A 12% (Fresenius Kabi, Bad Homburg, Germany). Finally, volume is adjusted to 200 mL with normal saline solution alone.

### Administration of MSCs

Patients undergo neuroleptoanalgesia and are monitored by an anesthesiologist. MSCs are administered by intra-arterial route, as already described [28], with modifications according to local equipment and local standards: with Seldinger technique, catheterization is carried out via the right common femoral artery (or the left one in the event of difficulty in achieving arterial access) using a 6 F Ultimum EV (St Jude Medical, Minnetonka, MN, USA) introducer and a 5 F Hinck or Simmons (Terumo Europe NV, Leuven, Belgium) diagnostic catheter. An angiographic study of the cervical and intracranial arteries is performed, with the support of a 0.035 inch, 150 cm long hydrophil guide (Terumo Europe NV, leuven, Belgium). Subsequently, with or without an exchange maneuver, using a 260 cm Starter exchange (Boston Scientific, Natick, MA, USA), a Mach 190 cm catheter guide (Boston Scientific, Natick, MA, USA) is used, after intravenous administration of a bolus of heparin sodium (3,000 to 5,000 IU according to body mass) to reduce the risk of thromboembolism. The catheter guide will be positioned in the widest vertebral artery. Subsequently, the main catheter is placed in both internal carotid arteries and a microcatheter is moved forward up to the widest vertebral artery.

The MSC are then injected into the various districts with an automated peristaltic pump, via the microcatheter. Should any ulcerated atherosclerotic plaques be found at carotid bifurcations, therapy is injected proximally to the lesion. Once therapy administration has been completed, MRI of the brain is performed with two sequences, FLAIR and DWI. Patients are closely monitored for 3 hours after the procedure and then moved to the Neurosurgery Unit, where they spend the next 24 hours. Provided that the procedure was uneventful, they are discharged the day after the cell injection. Patients undergoing the sham procedure are monitored in the same way.

### Motor status assessment

The patients undergo neurological examinations designed to assess motor function using the following scales:

Unified Parkinson’s Disease Rating Scale (MDS-UPDRS) total and motor score [31];

Hoehn and Yahr staging [32];

PSP rating scale [33] to specifically rate PSP severity;

SEADL (Schwab England Activities of Daily Living);

CGI (Clinical Global Impression for disease severity) [34];

If the patient is taking dopaminergic therapy, the neurological assessment is performed twice: in OFF upon wakening and in ‘ON’ after taking therapy in the morning by the same neurologist.

After patient’s consent, the entire neurological examination is video-recorded so that the evaluation can be performed again by assessors blind to allocation.

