**Methods/design:**

Autologous bone marrow (BM) mesenchymal stem cells (MSC) from patients affected by different type of parkinsonisms have shown their ability to improve the dopaminergic function in preclinical and clinical models. It is also possible to isolate and expand MSC from the BM of PSP patients with the same proliferation rate and immuphenotypic profile as MSC from healthy donors. BM MSC can be efficiently delivered to the affected brain regions of PSP patients where they can exert their beneficial effects through different mechanisms including the secretion of neurotrophic factors.

Here we propose a randomized, placebo-controlled, double-blind phase I clinical trial in patients affected by PSP with MSC delivered via intra-arterial injection.

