### Statistics

#### General considerations

As noted above, the safety of cellular therapy administration in the first five patients will be reviewed by the Data Safety Monitoring Board. These reviews will be shared with our institutional IRB. If the treatment appears safe, as determined by the Data Safety Monitoring Board with institutional IRB agreement, the protocol may be reopened to treat a total of 20 patients.

For statistical analysis of efficacy endpoints, descriptive statistics are computed for variables of interest (mean and SD for continuous variables and frequencies for categorical variables). Test results are summarized over time using appropriate graphical or tabular formats. The non parametric pair wise Wilcoxon rank sum test will be used to investigate each variable within subject and between the same subject at different follow-up (e.g. pre- vs. post-MSC, pre- vs. post-sham, etc.). The use of a non-parametric test has been considered the most appropriate since the distribution of the variable is not known and the number of observations is relatively small. For each time point, the test will be performed with 20 paired values (the values before and after MSC therapy in the 10 subjects allocated to immediate treatment plus the 10 subjects allocated to the delayed treatment).

P-values < 0,05 will be considered statistically significant. Additional summary statistics are also considered as appropriate to the data.

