#### Multifactorial movement analysis

The data related to each of the four tests will be normalized and the mean of the values related to each variable recorded during the 8 walks will be calculated. The data before and after MSC therapy will be compared using Wilcoxon’s signed rank test for matched pairs, considering the patients before and after treatment as a pair (the results at each follow-up visit will be assessed separately). Moreover, the results obtained in PSP patients will be compared with those obtained in the group of age-matched healthy volunteers using the non-parametric Mann–Whitney U Test.

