In this study a “pure” control group treated with placebo solution administered by the same route in a double-blinded manner is missing since this option was considered not acceptable by the ethical point of view by the investigators, given the potential harm of a cerebral artery catheterization procedure that is not justified by a potential benefit. Nevertheless, the patients enrolled in the control harm receive a simulated arterial catheterization and administration procedure and the neurologist and the neuro-radiologist who perform the follow-up evaluation are blinded. In this way, we exclude the placebo effect with the best precision.

In conclusions, the presented protocol is the first attempt to understand if MSC can be safely administered and can exert a beneficial effect in PSP patients. We believe that the results of this trial will help to improve the knowledge around the neuroprotective properties of MSC that might be exploited in other several neurodegenerative disorders.

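### The named efficacy test is an uncontrolled before/after-MSC comparison that allocation blinding only partly masks, so the claim to exclude the placebo effect and the abstract's design label go too far

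*Protocol article*

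**What the plan says.** - **Design (Study design).** After an open pilot phase, patients are randomized to MSC then sham, or sham then MSC. The second procedure comes 6 months after the first. Follow-up runs at least 12 months after MSC, for a total of 18 months.
- **Test (General considerations).** "For each time point, the test will be performed with 20 paired values", namely "the values before and after MSC therapy in the 10 subjects allocated to immediate treatment plus the 10 subjects allocated to the delayed treatment". The within-subject comparisons given as examples are "pre- vs. post-MSC, pre- vs. post-sham". No test of MSC against sham is named.
- **Movement analysis.** A matched-pairs test is planned, "considering the patients before and after treatment as a pair". The only between-group test compares patients with healthy volunteers.
- **Blinding.** Under Motor status assessment, the examination is filmed "so that the evaluation can be performed again by assessors blind to allocation". The Discussion adds that "the neurologist and the neuro-radiologist who perform the follow-up evaluation are blinded", without saying to what.
- **Label.** The abstract announces a "randomized, placebo-controlled, double-blind phase I clinical trial". The opening of Methods/design calls the same trial sham-controlled. The Discussion concedes that a control group "treated with placebo solution administered by the same route in a double-blinded manner is missing", yet goes on to say that the design rules out the placebo effect. The abstract's own discussion paragraph makes a similar promise.

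**The concern.** Blinding and sham protect a result only if the analysis compares MSC with sham. Here the named test compares patients with their own earlier state, and every patient eventually receives MSC. Three things other than an MSC effect can move such a difference: what patients expect, what raters expect, and the passage of time. Several of the listed scales rest on judgement.

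At stake is the efficacy conclusion. The article faults earlier open-label studies because beliefs of patients and investigators could have driven their improvements. A before/after-MSC test shares that weakness even when a sham arm exists, because the sham data do not enter it.

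**Working it through.** **Inputs.** The sequences, the 6-month delay and the 18-month duration are from Study design. The 10 + 10 patients and the 0.05 level are from General considerations. I assume a two-sided test (sidedness is not stated), that the test is the signed-rank form (the values are paired), that month-6 assessments precede the second procedure and serve as the delayed arm's pre-MSC values, and that raters know which visit they are scoring.

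**1. The plan's own figure.** 10 immediate + 10 delayed = 20 pairs. This agrees with the article.

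**2. What allocation blinding hides.** At month 0 nobody has had MSC. After the second procedure everybody has. Only in between does MSC status depend on the arm.

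| Months after MSC | Sequence | Before | After | Status before | Status after |
|---|---|---|---|---|---|
| 6 | immediate | 0 | 0 + 6 = 6 | known | hidden |
| 6 | delayed | 6 | 6 + 6 = 12 | hidden | known |
| 12 | immediate | 0 | 0 + 12 = 12 | known | known |
| 12 | delayed | 6 | 6 + 12 = 18 | hidden | known |

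No pair is hidden at both ends. Three of the four kinds are hidden at one end, and one kind at neither.

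**3. What each comparison estimates.** Write the mean change after MSC as E + P + R + T: MSC effect, patient placebo response, rater expectation and time trend.
- Before/after MSC estimates E + P + R + T.
- Sham change over months 0-6 estimates P + R + T, provided that patients find the sham convincing and raters are masked at month 6.
- MSC minus sham over months 0-6 therefore estimates E.

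A separate pre/post-sham test does not perform this subtraction.

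**4. Illustration.** Set E = 0 and let d = P + R + T, in SDs of the change score, equal in both arms. Changes are normal with SD 1, with 4000 simulated trials per row. The simulation error is at most √(0.25/4000) = 0.8 percentage points. The values of d are assumptions; the documents give none.

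| d | Signed-rank, 20 before/after pairs | Rank-sum, month 0-6 change, 10 vs 10 |
|---|---|---|
| 0 | 4% | 4% |
| 0.2 | 13% | 4% |
| 0.3 | 24% | 5% |
| 0.5 | 56% | 4% |
| 0.8 | 91% | 4% |
| 1.0 | 98% | 5% |

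**5. Precision given up.** With the same SD of change, the standard error of the mean change from 20 pairs is SD/√20 = 0.22 SD. For a difference of 10 versus 10 it is SD × √(1/10 + 1/10) = 0.45 SD, twice as large.

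**6. The label.** Abstract: placebo-controlled and double-blind. Methods: sham-controlled. Discussion: no placebo solution is given double-blind by the same route. The first statement cannot stand beside the other two.

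**The case against.** A reader might infer that allocation blinding does nothing for the tested result. The documents do not support that. In this two-sequence design it hides MSC status at month 6, which is one end of every 6-month pair and of the delayed arm's 12-month pairs.

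A reader might also infer that raters certainly know the visit order. The article does not say so: it is silent on how recordings are labelled and ordered, and on what the follow-up evaluators are blinded to. Such details, and the choice between live and video score as the analysed rating, may sit in the full protocol or the SAP. Their absence here is not a fault.

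The Motor function and Neuropsychological assessments sections promise only descriptive analysis, and the section-specific before/after test is for instrumented movement data, which no rater scores. This has weight. Still, General considerations applies its test to each variable, and even instrumented gait remains open to placebo response and time trend.

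The simulated rates could be read as this trial's false-positive rate. They are not. The Background describes a steadily disabling disease, so decline over 6 to 12 months would work against any drift toward improvement. The net shift may be smaller, absent or reversed.

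Finally, the Discussion does not say that blinding is absent. It describes a simulated procedure and blinded evaluators, and the sham is openly disclosed. The label fault lies in the abstract.

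None of this restores the missing MSC-versus-sham test. Complete masking of visit order would remove R from step 3, but leave P and T.

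**Conclusion.** The point holds in limited form. The named efficacy test is uncontrolled, and allocation blinding masks at most one end of any pair when the visit is known. The immediate arm's 12-month pairs are masked at neither end. The statements that the design excludes the placebo effect therefore do not follow from the named test. This conclusion needs no assumed bias: it follows from the test compared with the sequence design. The statement about masked ends does depend on raters knowing the visit, which the article neither states nor rules out.

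The size of the bias cannot be derived from the documents. The 24% to 56% range, for an assumed shared shift of 0.3 to 0.5 SD, shows how exposed the test is and predicts nothing about this trial.

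The conflict between the abstract's label and the rest of the article is plain from the text. Since safety is the primary objective and efficacy is explored only preliminarily, this should be corrected but does not undermine the trial's main purpose.

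**What to change.** 1. **Comparison.** Name the month 0-6 change, MSC versus sham (10 versus 10, assessed before the second procedure), as the efficacy comparison. Label before/after-MSC results descriptive. Confine any statement about blinding or excluding the placebo effect to that comparison.
2. **Rating.** For motor items that can be judged on film, have the already planned blinded assessors score recordings with date, visit and arm removed, in random order within and across patients. This removes rater expectation only, so it supplements step 1 and does not replace it.
3. **Wording.** Replace the abstract's label with sham-controlled, and state which roles are blinded, including whether patients are.

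**Cost.** Steps 2 and 3 need file relabelling, shuffling and text changes; the videos and assessors are already planned. Step 1 needs no new data, but its standard error is twice that of the 20 pairs, so the comparison should be presented as exploratory. Items that need touch or history cannot be scored from video and stay with the live blinded neurologist.

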### Multifactorial movement analysis

Patients perform four tasks:

(1.) upright standing;

(2.) starting to walk;

(3.) linear free gait (with and without a cognitive task);

(4.) gait along a curvilinear trajectory.

Tests are carried out in the order listed above as already described with minor modifications [35], if possible given the clinical status of the patient, before and after MSC therapy. Each test requires 4–8 walks, at intervals of about 5–10 minutes, on a platform about 10 meters long at a comfortable speed. The cognitive task consists in a calculation (counting backwards, starting from 100 and subtracting 7 at a time). The patients are not corrected or stopped if they make mistakes in calculating. The curvilinear test consists in straight walking for 2 meters towards the center of the platform and then a curvilinear trajectory with an angle of 90° for another 2 meters. Data are collected with a SMART optoelectronic movement analysis system (BTS SpA, Italy) equipped with: (i) optoelectronic system (six cameras with 60 Hz acquisition frequency) to establish the position of 29 reflecting markers applied onto the skin of the patients at anatomical landmarks (ii) three dynamometric platforms (KISLER, GmbH, Winthertur, Switzerland) with 960 Hz acquisition frequency to record ground reaction forces; (iii) TELEMG telemetric electromyograph (BTS SpA) and a FreeEMG wireless electromyography to measure muscular activity of tibialis anterior and soleus bilaterally.

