## Background

Progressive supranuclear palsy (PSP) is a rare form of parkinsonism with a prevalence of about 0.5 cases per 100,000 inhabitants and with an incidence of 5.3 new cases every 100,000 inhabitants [1,2]. Its etiology is unknown. From a pathological point of view, the disease consists in a neurodegenerative process that involves the basal ganglia, the brainstem, the prefrontal cortex and the cerebellum, with accumulation of a tau protein - hence the classification as tauopathy [3]. Onset typically occurs after 40 years of age. The symptoms include bradykinesia, proximal and axial rigidity and early postural instability. The key sign, which gives the disease its name, is the supranuclear paralysis of vertical gaze, followed by abnormalities of horizontal gaze. This sign usually appears three or four years after the onset of motor symptoms. The most disabling symptoms, especially in the early phases of the disease, are stiff, upright posture and abnormal gait with a very broad base associated with severe postural instability and frequent falls, especially backwards. The patient is confined to a wheelchair on average after 5 years of disease. Levodopa response is poor or absent [4-6]. Mean survival amounts to 7 years [7]. Early falls, speech and swallowing problems, diplopia and early insertion of a percutaneous gastrostomy are predictors of reduced survival [8].

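### Gait is tested only when the patient's condition allows and is analysed by a paired test at each visit, so patients who lose the ability to walk leave the test and the gait result leans toward apparent stabilisation

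*Protocol article*

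**What the plan says.** **Collection.** In Methods/design, under Multifactorial movement analysis, the standing and gait tasks are performed "if possible given the clinical status of the patient, before and after MSC therapy". The same paragraph states: "Each test requires 4–8 walks, at intervals of about 5–10 minutes".

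**Analysis.** Under the same title in the Statistics section, "the mean of the values related to each variable recorded during the 8 walks will be calculated". Before and after values then go into a "signed rank test for matched pairs, considering the patients before and after treatment as a pair", with each follow-up visit assessed on its own.

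**Number of pairs.** General considerations, in the Statistics section, says: "For each time point, the test will be performed with 20 paired values". These are 10 patients treated immediately plus 10 treated after the delay.

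**Who may lose gait.** Table 1 admits "Disease duration 12 months to 8 years" and requires 30 seconds of unaided standing, but no walking ability. The Background says: "The patient is confined to a wheelchair on average after 5 years of disease". Follow-up is at least 12 months after cell therapy, and the study lasts 18 months in all.

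**How the result is read.** The secondary objective counts either stabilisation or improvement of motor function as efficacy.

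**The concern.** Whether a gait value exists depends on the quantity being measured. A patient who worsens until the task is impossible has a baseline value and no follow-up value, and a signed rank test on matched pairs cannot use that patient. Because each visit is tested separately, values from the patient's other visits do not help.

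The patients lost this way are those with the worst outcomes, so the remaining pairs show less decline than the treated group experienced. A smaller, non-significant decline reads as stabilisation, which is a favourable result in this trial. With no true mean change, the same selection can produce a significant apparent improvement.

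A smaller matter sits beside this. The collection text allows four to eight walks, and the analysis text averages over eight. The value for a patient with four to seven walks is therefore not clearly defined.

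**Working it through.** **1. The plan's own figure.** 10 immediate + 10 delayed = 20 pairs. This holds only if all 20 patients have both a baseline and a follow-up gait value. If each patient independently has a 5%, 10% or 20% chance of having no follow-up value (assumed rates), the chance of 20 complete pairs is 0.95^20 = 36%, 0.90^20 = 12% or 0.80^20 = 1%.

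**2. What the text allows to be calculated.** The document gives no rate of untestable patients, no SD, no expected decline and no correlation between visits. The direction of the bias follows from the text; its size does not. The figures below illustrate it under stated assumptions.

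**3. Set-up.** 20 patients; normal baseline *b* and follow-up *f*, each with SD 1 and correlation ρ; change *c* = *f* − *b*, negative meaning worse.
- SD of change = √(2(1 − ρ)): 1.00 for ρ = 0.5 and 0.63 for ρ = 0.8.
- True mean change is −0.5 SD of change.
- The *k* patients with the lowest *f* cannot be tested.
- The test is the two-sided signed rank test at 0.05 on the remaining 20 − *k* pairs (the article does not state sidedness).

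**4. Results with a true decline of 0.5 SD of change.**

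| Worst patients lost | Decline seen, ρ = 0.8 | Decline detected, ρ = 0.8 | Decline seen, ρ = 0.5 | Decline detected, ρ = 0.5 |
|---|---|---|---|---|
| 0 of 20 | 0.50 | 54% | 0.50 | 55% |
| 2 of 20 | 0.45 | 44% | 0.41 | 40% |
| 4 of 20 | 0.39 | 30% | 0.34 | 25% |
| 6 of 20 | 0.36 | 24% | 0.26 | 16% |

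As a share of the true decline, 0.45/0.50 = 90% falling to 0.36/0.50 = 72% is seen for ρ = 0.8, and 0.41/0.50 = 82% falling to 0.26/0.50 = 52% for ρ = 0.5. Simulation error is one to two percentage points for detection. A fresh run gave the same pattern.

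**5. How much of the lost power is bias?** At ρ = 0.8, losing 4 patients at random lowers detection from 54% to 43%, a fall of 11 points. Losing the worst 4 lowers it to 30%, a fall of 24 points. So 11/24, or 46%, of the fall comes from fewer pairs and the rest from selection. The shrinkage of the estimate in step 4 comes from selection alone.

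**6. No true mean change.** Significant apparent improvement occurs in about 2.4% (ρ = 0.5) and 2.3% (ρ = 0.8) of runs with no loss. It rises to 8.9% and 6.4% with the worst 4 lost, and to 14.6% and 7.7% with the worst 6 lost.

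**7. The opposite extreme.** If the untestable patients are instead coded as the largest declines, and the true mean change is zero, significant decline appears in about 8% to 12% of runs with 4 coded and about 20% to 30% with 6, against about 2% with none. That coding has its own bias, so it cannot simply replace the completers' test.

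**The case against.** **This is missing detail that belongs in the analysis plan.** The article never says untestable patients are excluded, and a rule for them is often left to a fuller document. That is fair as far as a missing-data section goes, and its absence is not the point here. What the article does fix is conditional collection followed by a separate paired test at each visit. Followed as written, that excludes these patients.

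**Loss may be rare.** The standing requirement selects patients fitter than the disease average. This stands as a caution. A reader might set the eight-year duration limit against the five-year average to wheelchair and infer a loss rate, but the document supports no rate. It makes some loss plausible, since standing for 30 seconds is not a walking criterion and does not prevent later loss.

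**Other scales.** A reader might extend the bias to all motor outcomes. The text does not support this. The condition is attached only to movement analysis, and Motor status assessment, which covers the PSP rating scale, UPDRS, Hoehn and Yahr, SEADL and CGI, carries no such condition. Those scales can show deterioration in a patient who no longer walks.

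**Twenty pairs.** The figure can be read as planned enrolment, so stating that it is a maximum is editorial.

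**Four to eight walks.** A reader might infer that frailer patients with fewer than eight walks are discarded. The text does not link the number of walks to frailty, and averaging the walks recorded is the natural reading. The mismatch is real but small.

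**The illustration is severe.** It assumes that exactly the worst patients are lost, and part of the power loss would occur anyway. Both are true. Less selective loss gives a smaller bias in the same direction.

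**Conclusion.** The point holds for movement analysis. Conditional testing combined with per-visit matched pairs removes patients who lose gait, and biases the before–after result toward stabilisation, which the trial counts as efficacy. The direction follows from the text, provided that some patients become untestable through deterioration.

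The size is not known. With 2 to 6 of 20 lost from the bottom and a true decline of 0.5 SD of change, the decline seen is about 0.45 to 0.36 SD (correlation 0.8) or 0.41 to 0.26 SD (correlation 0.5). The loss numbers, the decline and the correlations are all assumptions.

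Gait is one of several secondary efficacy measures in a trial whose primary objective is safety. The change should be made, but the point does not undermine the trial as a whole.

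**What to change.** For movement analysis only:

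- Record the reason for every missed gait test.
- Report, per visit and arm, how many patients were tested and how many were unable to perform for clinical reasons.
- Keep the completers' signed rank test. Beside it, pre-specify a sensitivity analysis on within-patient differences, signed so that negative is worse. A patient testable at baseline but unable to perform at follow-up because of deterioration or death receives the largest negative difference, with such patients tied.
- Do not conclude that gait has stabilised unless both analyses agree.
- Define each value as the mean of all valid walks recorded (4 to 8), so that the collection and analysis paragraphs match.
- State in General considerations that the 20 pairs are a maximum.

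**Cost.** One added data field and some analysis wording. The sensitivity result is a composite without an effect size in gait units. It can overstate decline when inability is not due to disease progression, which is why the reason must be recorded and why it stands beside the main test and does not replace it.
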